#### Advisory committee

This committee will gather experts and decision-makers, who actively collaborate to this research project but are external to our institution, especially colleagues at the three fertility clinics of comparison. This committee will advise the research team on design of the intervention and planning of the evaluation, including evaluations on their sites. The Advisory committee will meet as needed and will be actively involved in revising documents and through informal communications. Post-intervention meetings will also serve as knowledge transfer activities.

#### Intervention sub-committee

This sub-committee will be in charge of developing the intervention in all its details and to follow-up closely on its implementation. This sub-committee will meet every month before the project begins and then as needed until the end of the intervention.

#### Evaluation sub-committee

This sub-committee will develop all the evaluation tools and will plan the qualitative evaluations. It will be particularly active before the start of the intervention and at the end of the intervention for the qualitative evaluations on all sites.

### Development & implementation of the lifestyle program for obese infertile women (Objective 1)

The Intervention sub-committee will be directly in charge of defining the intervention and planning the implementation. A complete review of the relevant literature will be performed initially and made available to all other committee members. The implementation of the program will be closely monitored by this sub-committee with evaluation of required human, material and other resources; barriers that will be encountered; potential solutions that will be applied; and discussion of difficult cases managed in the program. In addition, a specific qualitative evaluation of the program implementation will take place at the end of the intervention and will be planned by the Evaluation sub-committee. All women included in the CHUS RCT will be evaluated by questionnaires and a sub-group of 20 of these patients will be selected to participate in focus groups. In order to compare health professionals’ and patients’ satisfaction, perceptions and impact of the program on their life to those during usual care in Canada, we recruited three Canadian fertility clinics with different characteristics. In these clinics, 20 patients randomly selected will be evaluated at the end of the study using the same questionnaires and focus group methods. In all four centers, health care providers involved in the fertility clinic and/or the program will also be evaluated by questionnaires and focus groups.

This objective will be under the supervision of our Steering committee and Advisory committee.

Decision-makers from Quebec and Canada who sit on these committees will ensure that our program meets their objectives and is acceptable in terms of required resources and costs. Furthermore, we will validate our program design and evaluation plan with worldwide key experts as well as Canadian obesity experts contacted through the Canadian Obesity Network (CON). We will benefit from the experience of experts involved in the implementation and evaluation of similar programs: the Fertility Fitness program in Australia and the Lausanne Obesity-Fertility clinic in Switzerland.

### Evaluation of clinical outcomes of the lifestyle program for obese infertile women (Objective 2)

The **primary outcome** will be live-birth rates at 18 months. **Secondary outcomes** will be sub-divided into four categories of clinical outcomes:***Lifestyle and anthropometric outcomes***: evolution of anthropometric measures, changes in lifestyle habits (diet, exercise, sleep, alcohol, and tobacco), physical fitness level, daily energy expenditure from physical activities, time spent in various physical activity intensities, step count, evolution of readiness for change, quality of life.***Fertility outcomes***: pregnancy rate (biochemical pregnancy confirmed by a positive beta-human chorionic gonadotropin (β-hCG) level in the serum), spontaneous abortions, multiple pregnancies, spontaneous vs. ART-induced pregnancy, doses of fertility medications, number of treatment or IVF cycles.***Pregnancy adverse outcomes***: gestational diabetes, hypertension, pre-eclampsia, thromboembolism, caesarean section.***Neonatal outcomes***: birth weight, hypoglycemic episodes, Apgar score, jaundice, admission to neonatal intensive care, congenital defects, intrauterine death.

The results obtained at the CHUS will also be compared to those of women with the same criteria who will be seen in three fertility clinics across Canada. At the CHUS, primary and secondary outcomes will be determined using patients’ assessments, questionnaires and review of patients’ records. At the comparative clinics, charts of patients seen during the same time period will be retrospectively reviewed, and administrative data will be gathered.

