### Study participants

Study participants will be recruited among all women consulting at the CHUS fertility clinic. The staff will assist the research team in identifying potential participants. To be included in the study, women must fulfill the following inclusion criteria: 1) infertility; 2) aged between 18 and 40 years; and 3) obesity (BMI ≥30 kg/m^2^) or overweight if PCOS (BMI ≥27 kg/m^2^). Women will be excluded if they had bariatric surgery or plan for it and/or if natural conception is impossible or highly unlikely (tubal factor, severe male factor infertility, etc.). Infertility will be defined as: 1) failure to achieve a clinical pregnancy after 12 months or more of regular unprotected sexual intercourse in women who are under 35 years with regular menstrual cycles; 2) women who do not have regular menstrual cycles, or are older than 35 years and have not conceived during a 6-month trial period; or 3) women with a known cause of infertility. Eligible patients will be referred to the research coordinator to obtain their individual informed consent prior to baseline data collection.

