### Intervention

#### Control arm

Participants assigned to the control group will receive standard fertility treatments, which will be initiated as soon as clinically indicated. Standard fertility treatments may include lifestyle counselling by the obstetrician-gynecologist certified in gynecologic reproductive endocrinology and infertility (GREI), reproductive endocrinologist or fertility specialist in charge of the care of the patient.

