#### Intervention arm

Participants allocated to the intervention group will be invited to participate in the interdisciplinary lifestyle intervention and will have to delay other fertility treatments for six months. After 6 months of lifestyle intervention alone, women who are not pregnant will begin pharmacologic fertility treatments, as indicated, in conjunction with the lifestyle intervention that will continue to be offered. The aim of the intervention will be to implement progressive and sustainable lifestyle changes in order to reach a modest weight loss. Women will be invited to individually meet with a dietitian and a kinesiologist (20–30 min each) at 0, 3, 6 weeks and then every 6 weeks over a period of 18 months or until the end of pregnancy. A follow-up phone call/email will also take place once between each meeting for additional support. The dietitian will use 3-day food records to evaluate the women’s food intake throughout the program. To help improve patient’s diet, Canada’s Food Guide and the “Healthy Plate” [51] will be the main tools use for nutritional counselling. The kinesiologist will be responsible for taking anthropometric measures and vital signs and for coaching women to increase their physical activity level. A pedometer will be offered to assist the patient. Patients will be guided by the dietitian and the kinesiologist to formulate S.M.A.R.T goals (specific, measurable, attainable, realistic, and timely) at each meeting. The members of our interdisciplinary team will be trained in motivational interviewing. This training can positively affect the attitude to behaviour change in obese infertile women [52].

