#### Evaluation of anthropometric and lifestyle benefits and impact on fertility, pregnancy and neonatal outcomes (CHUS only) (Objective 2)

Evaluations of anthropometric measures and lifestyle habits will take place at baseline, prior to randomisation, and then every 6 months for 18 months. Among women who become pregnant, data will be collected, at the beginning of the pregnancy and at 24–28 weeks. If a woman becomes pregnant within a month of a standard evaluation visit, this visit will be considered as the first pregnancy visit. If a miscarriage occurs, the original follow-up will continue until 18 months or the end of another pregnancy. An overview of the study design and data collection is provided in Fig. 1.

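### Pregnancy rate rests on any positive serum β-hCG while fertility care differs by arm in months 0–6, so very early losses may be ascertained unequally

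*Protocol article*

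**What the plan says.** Under Objective 2 (evaluation of clinical outcomes), the fertility outcomes begin with "pregnancy rate (biochemical pregnancy confirmed by a positive beta-human chorionic gonadotropin (β-hCG) level in the serum), spontaneous abortions". Table 2 repeats the serum β-hCG as the source for pregnancy rate, collected throughout the study. It takes the other fertility outcomes from the medical record.

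The arms are managed differently at first. Under Control arm, women receive "standard fertility treatments, which will be initiated as soon as clinically indicated". Under Intervention arm, women "will have to delay other fertility treatments for six months", and "After 6 months of lifestyle intervention alone, women who are not pregnant will begin pharmacologic fertility treatments, as indicated".

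β-hCG is one of the analytes in the fasting panel described under Blood sample. The study evaluations "will take place at baseline, prior to randomisation, and then every 6 months for 18 months". Women who become pregnant have further visits at the beginning of pregnancy and at 24–28 weeks.

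Only the intervention arm has programme contacts. Individual meetings with a dietitian and a kinesiologist take place "at 0, 3, 6 weeks and then every 6 weeks over a period of 18 months or until the end of pregnancy", with a call or email between meetings and 12 weekly group sessions.

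Data analyses and interpretation plans time-to-event analyses for fertility outcomes, censored at drop-out alone.

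**The concern.** A biochemical threshold counts conceptions that may end within days of a missed period. Such an event enters the data only if blood happens to be drawn in a short window. A six-monthly panel will miss most of them. The early-pregnancy visit does not help, because it takes place only once a pregnancy is known. Recording therefore depends mainly on tests drawn in the course of care, and in months 0–6 the protocol makes care differ by arm.

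If one arm is tested more often, it gains recorded pregnancies, and earlier recorded dates, without any real difference in fertility. If biochemical losses are counted as spontaneous abortions, it gains recorded miscarriages as well. Pregnancy rate and spontaneous abortion are named secondary outcomes, and better fertility is part of the first hypothesis, so readers will give these comparisons weight.

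**Working it through.** **The plan's own figures.** No figure is stated for pregnancy rate, miscarriage rate or frequency of β-hCG testing. The one power statement concerns live birth: 25 % against 50 %, α 5 % (taken as two-sided), 80 % power. It reproduces at 58 per group (power 0.802, pooled variance, no continuity correction) and does not bear on this point.

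**Model.** Conception and loss are truly identical in both arms; only detection of biochemical losses in months 0–6 differs. Every input is an assumption; none comes from the documents.

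- T = conceptions per woman, 0.5 to 0.6
- b = share of conceptions lost at the biochemical stage, 0.15 to 0.25
- f = share of conceptions arising in months 0–6, 0.20 to 0.50
- d = probability that a biochemical loss in months 0–6 is detected, which varies by arm
- detection of biochemical losses after month 6 = 0.9 in both arms
- clinical loss = 10 % of the remaining pregnancies

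With D = 0.9(1 − f) + f·d:

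- Recorded pregnancies = T(1 − b) + T·b·D
- Losses per recorded pregnancy = [b·D + 0.10(1 − b)] / [(1 − b) + b·D]

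The difference in recorded pregnancies, intervention minus control, reduces to T·b·f·(d_I − d_C).

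- Smallest non-zero case: 0.5 × 0.15 × 0.20 × 0.3 = 0.0045, or 0.45 points.
- Largest case: 0.6 × 0.25 × 0.50 × 0.6 = 0.045, or 4.5 points.

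Losses per pregnancy in the largest case (b = 0.25, f = 0.50):

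- Control, d = 0.9, D = 0.9: (0.225 + 0.075)/(0.75 + 0.225) = 30.8 %
- Intervention, d = 0.3, D = 0.6: (0.15 + 0.075)/(0.75 + 0.15) = 25.0 %
- Difference: −5.8 points

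| Detection in months 0–6, control / intervention | Pregnancy rate, points | Losses per pregnancy, points |
|---|---|---|
| 0.9 / 0.9 | 0 | 0 |
| 0.9 / 0.6 | −0.45 to −2.25 | −0.7 to −2.8 |
| 0.9 / 0.3 | −0.9 to −4.5 | −1.4 to −5.8 |
| 0.6 / 0.9 | +0.45 to +2.25 | +0.7 to +2.8 |

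The last column applies only if biochemical losses count as spontaneous abortions and biochemical pregnancies form the denominator.

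**Extreme case.** Assume 40 % clinical pregnancy in both arms, half of the intervention arm's arising in months 0–6. Assume also that all early losses are detected except those in the intervention arm in months 0–6, where none are. Recorded rates are 0.40/(1 − b) for control and 0.20 + 0.20/(1 − b) for intervention:

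- b = 0.10: 44.4 % against 42.2 %, gap 2.2 points
- b = 0.20: 50.0 % against 45.0 %, gap 5.0 points
- b = 0.30: 57.1 % against 48.6 %, gap 8.6 points (from unrounded rates)

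**Overstatement in both models.** Each treats conceptions as if they were women. The article continues follow-up after a miscarriage, so a woman whose early loss is missed but who conceives again is still counted. The per-woman gap would be smaller.

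**Scale.** With 128/2 = 64 per arm and a rate near 50 %, the standard error of the difference is √(2 × 0.5 × 0.5/64) = 8.8 points. A bias of 4.5 points is about half of one standard error (4.5/8.8 = 0.51).

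**The case against.** The strongest reply is that the mechanism is inferred. Nothing in the article ties β-hCG tests to treatment cycles, and control treatment starts when indicated, not necessarily at once. The intervention arm has frequent contacts in months 0–6, each an opportunity to report a missed period and be tested. No matching contacts are listed for controls. This stands, and it removes any claim about direction. It does not rescue the definition: those contacts are dietary, exercise and psychology sessions with no serum test attached, and if they did raise testing, the comparison would still depend on who was tested.

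Several other limits also stand. From month 6 both arms may be treated, both share the six-monthly panel, and live birth is untouched. The article lists spontaneous abortion as a separate outcome taken from the record, so the miscarriage effect is conditional. A testing schedule or counting rule may exist in the full protocol, which is not shown. The point here is the definition that the article does state.

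A reader might also infer that the biochemical outcome contradicts the infertility criterion under Study participants, "failure to achieve a clinical pregnancy after 12 months or more of regular unprotected sexual intercourse". It does not. That wording concerns history at entry and appears in only one of three alternative limbs. An entry criterion does not fix how an outcome is defined.

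**Conclusion.** The concern holds as a risk of differential ascertainment, not as demonstrated bias. A biochemical threshold, early care that differs by arm, and no common β-hCG schedule in the article between six-monthly visits together leave pregnancy rate and time to pregnancy open to detection bias. Spontaneous abortion is affected too if biochemical losses are counted there.

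Under assumed partial detection the spurious difference in pregnancy rate is roughly 0.5 to 4.5 points, with either sign possible. That is modest against the sampling error of a trial of this size.

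A reader might infer that control pregnancies are certainly over-counted, or that the gap reaches 2.2 to 8.6 points. The documents do not support either. They do not say which arm is tested more, and the larger range needs complete detection against none and no later conception in women with a missed loss. The primary outcome and its sample size are unaffected.

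**What to change.** Define the fertility outcome for the between-arm rate and the time-to-event analysis as clinical pregnancy documented in the medical record, with the event date set by the same rule in both arms. Use clinical pregnancies as the denominator for spontaneous abortion. Report biochemical pregnancies and biochemical losses separately as supportive, and state that the latter are not counted as spontaneous abortions.

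In the model above this removes the spurious difference, because the arms differ only in detection of biochemical losses. A single β-hCG schedule applied to both arms would do the same, but needs extra blood tests.

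The cost is a change of wording and somewhat fewer pregnancy events. The chart review is already planned; that the record holds confirmation of clinical pregnancy is an assumption, since the article does not say so.

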### Cost-effectiveness assessment of the lifestyle program for obese infertile women (Objective 3)

Data collected for this objective will trace the operating costs (human and material resources) for each of the patients in the study based on two viewpoints: 1) the costs for the public health system; and 2) the costs for the patients. The two viewpoints will translate into two models of costs for all analyses. The key variable of interest is the total cost per live birth. This variable will be measured in two ways: 1) the total cost per infant alive for all women, which considers costs of unsuccessful interventions; and 2) the total cost per infant alive only for the women who had a live birth. Costs will include:

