#### Costs of adverse events or complications

*Health care system viewpoint* – Costs of hospitalization or drugs for adverse events related to the lifestyle program, fertility treatments, pregnancy or neonatal care. *Patients’ viewpoint* – Costs for transportation, parking, loss of salary, daycare, drugs not covered, incurred by the patients due to these adverse events or complications.

Data collection will be performed through patients’ charts review, administrative data, questionnaires and interviews with health care providers and staff of fertility clinics for the description of care procedures, as well as questionnaires to patients. At the CHUS fertility clinic, costs will be obtained prospectively and all patients will answer a specific questionnaire; but for the three fertility clinics of comparison, patients’ charts will be retrospectively reviewed. However, as mentioned, a sample of 20 patients will be selected for focus groups: these patients will also answer the same cost questionnaire. Thus, the exact costs from the patients’ viewpoint of the different events will be determined based on these 20 patients and then be extrapolated to the other patients. Departments or directorates of service (billing services at the CHUS, pharmacies, Human Resources, Department of Nursing) will be consulted to match each event to its monetary cost. Where possible, we will use the overhead costs, provided by the administrative services, for a particular treatment and/or complication. When this is not possible, we will conduct interviews with relevant professionals to track the various human resources and materials that were involved.

Since provincial and state pricings for the different outcomes are different, we will only consider a single reference price for each outcome, i.e. pricing in the Quebec health system. In order not to incur double counting in calculating the cost of primary outcome, we will make sure to check the reason for the expense and we will record every cost only once for the primary outcome. Regarding the joint use of equipment or spaces, the cost used will be the unit cost of depreciation for each use or visit. To the extent that the cost measure will be done over a period exceeding one year, we will use a discount rate. The reference discount rate will be 5 % per year. To test the robustness of our results, we also do a sensitivity analysis with rates of 3 and 8 %.

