### Sample size

Our sample size estimation is based upon our primary outcome (see Objective 2), which is live-birth rates between randomized groups at the CHUS. Based on the Fertility Fitness Program, the inclusion of 58 women per group will provide our study a power of 80 % to identify a doubling in live-birth rates with our program (25 to 50 %, α = 5 %). Assuming a dropout rate of 10 % (these women are usually highly motivated), our final estimated sample size will be 128 women. For other objectives and outcomes, it would be difficult to assess power because similar evaluations have not been previously reported.

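### The key economic variable, total cost per live birth, has two co-equal definitions, both per infant alive; one of them leaves out every woman without a birth

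*Protocol article*

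**What the plan says.** The Protocol article's section on Objective 3 states: "The key variable of interest is the total cost per live birth". It then gives two ways of measuring it:

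- Version 1: "the total cost per infant alive for all women, which considers costs of unsuccessful interventions".
- Version 2: "the total cost per infant alive only for the women who had a live birth".

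Both are per infant. The section ranks neither above the other and gives no rule for multiple births. Each is to be produced from two viewpoints, the public system and the patient.

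Other sections bear on this:

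- The primary outcome "will be live-birth rates at 18 months" (Objective 2). The Sample size section treats it as a proportion of women, 25 % against 50 %.
- Multiple pregnancy is recorded separately among the fertility outcomes: "spontaneous abortions, multiple pregnancies, spontaneous vs. ART-induced pregnancy".
- Women in the intervention arm "will have to delay other fertility treatments for six months"; control women face no such delay (Intervention arm, Control arm).
- The numerator includes "Costs of hospitalization or drugs for adverse events related to the lifestyle program, fertility treatments, pregnancy or neonatal care" (Costs of adverse events or complications).
- Hypothesis 2 predicts a lower cost per live birth, and the Discussion expects a significant reduction in it.

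**The concern.** Hypothesis 2 can be judged on either version, and the two can disagree.

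Version 2 conditions on having had a live birth, which is the endpoint that the intervention is meant to change. Women who reach it under the programme and women who reach it under control are not exchangeable groups, so randomisation no longer protects the comparison. The cost of treating women who did not have a birth also disappears. A programme that works by producing more births per woman treated gets no credit for that in this version.

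Version 1 has no such selection, but its unit differs from that of the primary outcome. One woman delivering twins is one success in the live-birth rate and two units in the cost ratio. If multiple births differ between arms, the cost ratio moves although no additional woman has a live birth. A difference is plausible because the arms start fertility treatment at different times.

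At stake is the economic result that the article directs at decision-makers.

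**Working it through.** **Inputs from the Protocol article.** Live-birth rates of 25 % (control) and 50 % (programme), 58 women per group, 80 % power, 10 % dropout, 128 in total (Sample size).

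**Assumptions.** The article gives no cost per woman and no twin share. I use 10,000 units per woman for illustration, and a range of twin shares.

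**The plan's own figure.** The usual two-proportion formula (pooled variance under the null, two-sided 5 %, 80 % power) gives 58 per group at 25 % against 50 %, with power 80.2 %. Then 116 × 1.10 = 127.6, or 128, which is 64 per arm. The figure reproduces when the outcome is one yes/no result per woman, which confirms that the unit of the primary outcome is the woman.

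**Version 2 at the planned rates, no twins, equal cost per woman.**

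| | Control | Programme |
|---|---|---|
| Women | 64 | 64 |
| Women with a live birth | 16 | 32 |
| Total cost, all women | 640,000 | 640,000 |
| All costs / women with a birth | 40,000 | 20,000 |
| Version 2 | 160,000 / 16 = 10,000 | 320,000 / 32 = 10,000 |
| Share of cost discarded | 48/64 = 75 % | 32/64 = 50 % |

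The twofold difference vanishes. If a woman without a birth costs 0.5 to 1.5 times as much as a woman with one, the discarded share is 60 % to 82 % in control and 33 % to 60 % in the programme arm. The all-women ratio is then 25,000 against 15,000 (at 0.5) or 55,000 against 25,000 (at 1.5). Version 2 stays at 10,000 in both arms throughout.

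**Direction.** At these rates there are 48/16 = 3 women without a birth per woman with one in control, and 32/32 = 1 in the programme arm. With equal cost per woman with a birth, leaving out failures helps the programme only if each of its failures costs more than three times a control failure.

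**Version 1 and twins.** With twin share t of deliveries, infants = deliveries × (1 + t), so cost per infant = cost per delivery / (1 + t). At equal cost and equal delivery rate per woman, the high-twin arm relative to the other is:

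- 20 % against 5 %: 1.05 / 1.20 = 0.875, or 12.5 % cheaper
- 10 % against 3 %: 1.03 / 1.10 = 0.936, or 6 % cheaper
- 25 % against 5 %: 1.05 / 1.25 = 0.84, or 16 % cheaper

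**Twin costs in the numerator.** Let a twin delivery cost x more than a single one. Starting from D single deliveries and total cost C, the cost per infant is (C + Dtx) / (D(1 + t)). This is below C/D only if x < C/D. At equal cost per woman, C/D is 4 times the mean cost per woman at a 25 % birth rate and 2 times at 50 %. Below that threshold the extra cost offsets part of the apparent saving; above it, the saving is gone.

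**Twins at the planned rates.** With 20 % twins in control and 5 % in the programme arm, and equal cost per woman: 40,000 / 1.20 = 33,333 against 20,000 / 1.05 = 19,048. The programme looks 1 − 19,048/33,333 = 43 % cheaper instead of 50 %. A reversal would need 1 + t(control) > 2 × (1 + t(programme)), which twins alone cannot produce, since t is at most 1.

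**The case against.** The strongest reply is that the article is open about both measures. Version 1 comes first, covers all women and expressly keeps unsuccessful treatment. Version 2 is plainly labelled as restricted. Costs are traced per patient and multiple pregnancies are recorded, so a per-woman ratio can be computed whenever it is wanted. This stands, and it limits the harm. It does not settle which figure tests Hypothesis 2.

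A reader might also infer more than the document supports:

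- *That neither version answers Objective 3 because both are average ratios.* Objective 3 asks first for cost per live birth compared with the control group, and also allows other cost-effectiveness measures. QALYs are planned. The form of an incremental ratio and its uncertainty analysis are details that an article may leave to the fuller plan.
- *That the programme could win because failures are left out.* At the planned rates control has more failures, so leaving them out favours control.
- *That control is bound to have more twins.* The different start of fertility treatment makes this plausible. However, programme women who have not conceived begin treatment at six months, with 12 of the 18 months left, and no twin rate is given.
- *That twins could overturn the result.* At the planned rates and equal cost per woman they could not, and costlier twin deliveries enter the numerator.

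**Conclusion.** The point holds as a defect in how the key variable is fixed: two co-equal definitions, neither named as main, and both in a different unit from the primary outcome.

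Version 2 is the more serious. It conditions on the primary endpoint after randomisation, and at the planned rates with equal cost per woman it turns 40,000 against 20,000 into no difference. Where women without a birth cost 0.5 to 1.5 times as much as women with one, Version 2 still shows no difference.

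The twin effect in Version 1 is smaller: about 6 % to 16 % over the assumed twin shares, at equal cost and equal delivery rate per woman, before any offset from twin and neonatal costs. It would matter most if the arms turned out close in live-birth rate and cost. The twin shares and unit costs are my assumptions, because the article gives none.

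**What to change.** In the Objective 3 section:

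1. Name one main measure, for each viewpoint: total cost of all randomised women divided by the number of women with at least one live birth.
2. Keep cost per infant alive, over all women, as a secondary measure. It shows the value of a second infant, which the main measure does not credit.
3. Label the cost among women who had a live birth as descriptive, and state that it is not a between-arm test of Hypothesis 2.
4. Optionally, report the incremental cost per additional woman with a live birth as one of the other cost-effectiveness measures that Objective 3 already allows.

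The cost is minor rewording of the analysis. Costs, births and multiple pregnancies are already to be collected, so no new data are needed.
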